### **3. Aim**

This a multicenter, prospective, randomized, controlled trial which enrolling patients with HF, left ventricular ejection fraction (LVEF)  $\leq 35\%$ , and LBBB. Patients will be randomly assigned in a 1:1 ratio to receive either LBBP or BVP. The clinical endpoints (including primary and secondary endpoints) will be compared between the

two groups to evaluate the effectiveness and safety, in order to provide new treatment methods for such patients and improve their prognosis.

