## **11. Statistical consideration**

### **11.1 Sample size calculating**

There are no studies evaluating the long-term prognosis of LBBP, and results for the long-term prognosis of BVP vary among studies. Therefore, the data for the sample size estimation of this study are mainly derived from our preliminary clinical experience. A sample size of 190 patients is calculated to detect a statistically

significant difference in the primary endpoint with 80% power and two-tailed alpha level of 5%, assuming 10% event rate in the LBBP and 25% in the BVP arm with 10% dropout and 5% crossover. To ensure sufficient statistical efficiency, the sample size is finally determined to be 100 for each group.

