### **5.2 Secondary endpoints**

The Secondary endpoints including: (1) Individual outcomes of all-cause mortality; (2) individual outcomes of HFH; (3) Echocardiographic response/super-response rates at 6-month follow-up. Echocardiographic response is defined as an absolute improvement in left ventricular ejection fraction (LVEF)  $\geq 5\%$ . Super-response is

defined as an absolute improvement in LVEF  $\geq 15\%$  or improvement of LVEF to  $\geq 50\%$ .

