## **8. Statistical Consideration**

### **8.1 Sample size calculating**

There are no studies evaluating the long-term prognosis of LBBP, and results for the long-term prognosis of BVP vary among studies. Therefore, the data for the sample size estimation of this study are mainly derived from our preliminary clinical experience. A sample size of 190 patients is calculated to detect a statistically significant difference in the primary endpoint with 80% power and two-tailed alpha

level of 5%, assuming 10% event rate in the LBBP and 25% in the BVP arm with 10% dropout and 5% crossover. To ensure sufficient statistical efficiency, the sample size is finally determined to be 100 for each group.

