## 8.3 Statistical analysis

All analyses in this study will be conducted according to the intention-to-treat principle. Student's t-test is performed for normally distributed continuous variables while Wilcoxon signed rank test is for non-normally distributed data. The chi-square test or Fisher exact test is used for categorical variables. A two-sided P-value  $< 0.05$  is considered statistically significant.

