## 8.5 Subgroup analysis

Subgroup analyses of the relationship between the primary endpoint and the baseline characteristics including age, sex, etiology, comorbidities, QRS duration, New York Heart Association (NYHA) class, and LVEF will be conducted.

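### One two-sided P < 0.05 rule covers every test, with no gate, testing order, adjustment or exploratory label for the four secondary endpoints or the subgroup analyses

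*Supplement*

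**What the plan says.** The plan names one primary endpoint, the composite of all-cause mortality and HFH (protocol v1.1 section 9.1; SAP section 6, numbered 5.1). The sample size is tied to it alone: "A sample size of 190 patients is calculated to detect a statistically significant difference in the primary endpoint", at 80% power and two-tailed 5% (SAP 8.1, protocol 11.1).

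The secondary endpoints follow under their own heading: "The Secondary endpoints including: (1) Individual outcomes of all-cause mortality; (2) individual outcomes of HFH; (3) Echocardiographic response/super-response rates at 6-month follow-up". The third item holds two rates, so there are four tests. The protocol summary table lists the same four.

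SAP 8.5 adds "Subgroup analyses of the relationship between the primary endpoint and the baseline characteristics including age, sex, etiology, comorbidities, QRS duration", and continues with NYHA class and LVEF. That makes seven headings, one of which (comorbidities) covers more than one condition. It names no test, interaction term or cut-point.

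The only decision rule is in SAP 8.3: "A two-sided P-value $< 0.05$ is considered statistically significant". Protocol 11.2 repeats it directly after its subgroup sentence. Protocol section 3 gives the aim in general terms: "The clinical endpoints (including primary and secondary endpoints) will be compared between the" two groups, to evaluate effectiveness and safety.

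**The concern.** The 5% alpha is designed around one comparison, but the rule that turns a P-value into a declared result is the same for all of them. The labels primary and secondary do not say how a secondary result may be used once the primary is known. Followed as written, the plan lets the trial report a significant effect on mortality, HFH, response or super-response after a null primary, and nothing tells the reader to treat it differently from a confirmed result. The same holds for a P-value from a subgroup analysis.

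What is at stake is the standing of the secondary and subgroup results. The primary conclusion is not affected.

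**Working it through.** **Inputs from the documents.** Per-test level 0.05 two-sided (SAP 8.3, protocol 11.2); four secondary tests (SAP 5.2, protocol 9.2); 100 patients per group (SAP 8.1). The calculated sample size of 190 does not enter this check.

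**Inputs that are assumed.** No treatment effect on any secondary. The correlation ρ between the four test statistics is not in the documents, so a range is shown.

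**Step 1. The plan's own figure.** The stated 5% is a per-test level. For one test, 1 − (1 − 0.05) = 5%. This is what the primary carries, and nothing below changes it.

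**Step 2. Four independent tests.** P(at least one) = 1 − (1 − 0.05)^4 = 1 − 0.8145 = 18.5%.

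**Step 3. Four equally correlated tests.** Write each statistic as Z = √ρ·W + √(1−ρ)·E, with W shared and E separate. Then

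P(at least one) = 1 − ∫ [Φ((1.96 − √ρ·w)/√(1−ρ)) − Φ((−1.96 − √ρ·w)/√(1−ρ))]^4 φ(w) dw.

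| ρ | P(at least one of four) |
|---|---|
| 0 | 18.5% |
| 0.2 | 18.0% |
| 0.3 | 17.4% |
| 0.5 | 15.6% |
| 0.7 | 13.0% |
| 0.9 | 9.4% |

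**Step 4. This trial's endpoint structure.** Null trials of 200 patients were simulated (8,000 per scenario), with log-rank for death and HFH and chi-square for the nested response rates. Event hazards, frailty and LVEF distribution are assumptions; three scenarios were run. Single tests rejected in 4.3% to 6.0% of trials. The response and super-response statistics correlated at about 0.44; death and HFH at 0.02 to 0.17. At least one of the four secondaries was significant in 17.6% to 18.5% of trials.

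**Step 5. The failed-primary case.** In the same simulations, any of the five tests (primary plus four) was significant in 19.0% to 20.1% of trials, and the primary alone in 5.0% to 5.2%. The difference is the chance that the primary is not significant but some secondary is: 20.1% − 5.2% = 14.9% in the scenario with least correlation, and 19.0% − 5.0% = 14.0% in the one with most.

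**Step 6. Effect of the remedy.** If secondaries count only after a significant primary, a false secondary claim needs both; this occurred in about 3.6% of simulated null trials. With the primary null it cannot exceed the primary's 5%. Within the four, Holm's first step uses 0.05/4 = 0.0125; for independent tests 1 − (1 − 0.0125)^4 = 4.9%.

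**Subgroups.** No figure follows from the plan, because SAP 8.5 fixes neither the test nor the number of tests.

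**The case against.** The strongest reply is that no promise is broken. The plan sets 5% for the primary and a per-test threshold elsewhere; it never undertakes to hold a family-wise 5% over the secondaries. One primary is named, the secondaries have their own heading, the sample size rests on the primary alone, and no passage says a secondary may establish success. Mortality and HFH are also components of the composite and help to interpret it. All of this stands, and it limits the size of the point. It does not supply the missing rule: no sentence says what happens to a secondary P below 0.05 when the primary fails.

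Four stronger readings are tempting, and the documents do not support them.

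- A reader might infer that a false secondary result is three times as likely as the stated 5%. Each test keeps about 5%; the higher figure is for at least one of four with all four null. A multiple of three also needs a correlation near 0.5, which the documents do not give.
- A reader might attach a figure to the subgroups, such as 30% for seven independent tests. That assumes one test per factor, which the SAP does not define.
- A reader might think the echocardiographic endpoints more prone to a lone false positive because they have more events. Under no effect they reject at about the same 5% as the others.
- A reader might take protocol section 3 to mean that a secondary can prove effectiveness. It is a general aim, not a decision rule.

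**Conclusion.** The point holds as a gap in the decision rule. One threshold applies to everything, and neither the SAP nor protocol v1.1 ranks, gates, adjusts or labels the secondary and subgroup results. With no effect on any secondary, the chance of at least one declared significant result among the four is about 13% to 18.5% for correlations of 0.7 to 0, falling to 9.4% at 0.9. Simulation under assumed event rates and LVEF changes sits at the upper end, and most of that chance falls in trials where the primary is not significant. The omission is certain from the text; the percentages depend on the assumed correlation and the global null. The subgroup share cannot be quantified. The primary test, its 5% error and the sample size are untouched, so this is an inexpensive improvement and not a fault in the main comparison.

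**What to change.** In SAP 8.3 to 8.5 and protocol 11.2, replace the blanket sentence with three statements:

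1. The trial is decided by the primary composite at two-sided 5%.
2. Secondary endpoints are tested for significance only if the primary is significant. They are tested either in a fixed order, each at two-sided 5% and stopping at the first non-significant result, or by Holm across the four. The sponsor chooses the method and any order before unmasking. Otherwise they are reported as exploratory.
3. Subgroup analyses are exploratory, and no claim of significance is made from them.

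A plain statement that all secondary and subgroup results are exploratory would also close the gap, at the price of giving up any confirmatory secondary claim.

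The cost is a few sentences, with no added patients or data. If exploratory results are to carry confidence intervals, an effect measure must also be named for the time-to-event endpoints, because SAP 8.4 lists only Kaplan-Meier curves and the log-rank test. The downside is that a lone secondary P just below 0.05, after a failed primary or a failed earlier step, can no longer be called significant.

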## 8.4 Statistical analysis of the endpoints

For the clinical endpoint, Kaplan-Meier (KM) survival curve and log-rank test are performed to compare the time-to-event between LBBP and BVP.

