## **3. Study Design**

This a multicenter, prospective, randomized, controlled trial which enrolling patients with HF, left ventricular ejection fraction (LVEF)  $\leq 35\%$ , and left bundle branch block (LBBB). Patients will be randomly assigned in a 1:1 ratio to receive either LBBP or BVP. Follow-up visits will be conducted at 1 month, 3 months, 6 months and every 6 months thereafter after surgery to evaluate the clinical endpoints (including primary and secondary endpoints) of the two groups.

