## **6. Study Endpoints**

### **5.1 Primary endpoint**

The primary endpoint is the composite of all-cause mortality and heart failure hospitalization (HFH). HFH is defined as any urgent visit with heart failure (HF) signs or symptoms requiring intravenous diuretic therapy.

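### Heart failure hospitalization alone has only Kaplan-Meier and log-rank planned and no rule for a prior death, so its incidence curve would read slightly too high

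*Supplement*

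**What the plan says.** SAP 8.4 is a single sentence. It begins "For the clinical endpoint, Kaplan-Meier (KM) survival curve and log-rank test are performed" and gives the purpose as comparing time to event between the two arms. Protocol v1.1, section 11.2, plans the same.

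SAP 5.2 (printed under Section 6) lists "individual outcomes of HFH" as a secondary endpoint, separate from all-cause mortality; protocol v1.1, section 9.2, does likewise. SAP Section 3 says that visits serve to "evaluate the clinical endpoints (including primary and secondary endpoints) of the two groups", so the term clinical endpoint is not confined to the composite.

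The event itself is defined without reference to death: "HFH is defined as any urgent visit with heart failure (HF) signs or symptoms requiring intravenous diuretic therapy".

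Neither document gives a censoring rule, says what happens to a patient who dies without an HFH, or names a method for competing events.

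**The concern.** A patient who dies without an HFH can never have one. Kaplan-Meier recognises only events and censored times. For HFH alone, death must therefore be treated as censoring, because counting it as an event would turn the curve back into the composite. Censoring at death treats those patients as if they could still be hospitalized later. One minus the curve then describes a setting in which nobody dies, and it lies above the probability of HFH that patients actually face.

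Death before HFH is to be expected here. Patients have LVEF of 35% or less and NYHA class II to IV, and the trial runs about four years with 1.5 years of recruitment, so follow-up is roughly 2.5 to 4 years each. Readers will use the HFH curve to see what lies behind the composite. If the trial's hypothesis is right, the BVP arm has more of both events, the overstatement is larger there, and the HFH difference is stretched in favour of LBBP.

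**Working it through.** **Inputs from the plan.** SAP 8.1 sizes the trial "assuming 10% event rate in the LBBP and 25% in the BVP arm with 10% dropout and 5% crossover", with 100 patients per arm. The plan states no HFH incidence and no mortality rate, so there is no HFH figure to reproduce.

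**Assumptions.** The share *a* of first composite events that are deaths is not given; 30% is used, with a range of 20% to 50%. Cause-specific hazards are taken as proportional over time. The composite rates are used as they stand, without dropout or crossover.

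**Formulas.** For composite risk *C*, the cumulative composite hazard is −ln(1 − C), and the HFH part is (1 − a) times that.

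- HFH incidence with death competing: (1 − a) × C
- One minus Kaplan-Meier, deaths censored: 1 − exp[(1 − a) × ln(1 − C)]

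**At a = 30%.**

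- BVP: −ln(0.75) = 0.2877; × 0.7 = 0.2014; 1 − exp(−0.2014) = 18.24%. Incidence is 0.7 × 25% = 17.50%. Excess 0.74 points.
- LBBP: −ln(0.90) = 0.1054; × 0.7 = 0.0738; 1 − exp(−0.0738) = 7.11%. Incidence is 0.7 × 10% = 7.00%. Excess 0.11 points.
- Difference between arms: 10.50 points becomes 18.24 − 7.11 = 11.13 points.

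**Over the range** (each cell: incidence → one minus Kaplan-Meier).

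| Death share (assumed) | LBBP | BVP | Difference, points |
|---|---|---|---|
| 20% | 8.00% → 8.08% | 20.00% → 20.56% | 12.00 → 12.48 |
| 30% | 7.00% → 7.11% | 17.50% → 18.24% | 10.50 → 11.13 |
| 50% | 5.00% → 5.13% | 12.50% → 13.40% | 7.50 → 8.27 |

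Whatever the death share, under proportional hazards the excess peaks at about 0.13 points in LBBP and 0.90 in BVP.

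**Bound without proportional hazards.** If every death came before every HFH, with *d* the proportion dying first and *h* = C − d, the excess would be h × d/(1 − d). Its maximum is 0.26 points at C = 10% and 1.79 points at C = 25%.

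**What drives the excess.** At rates in this range it rises with both event rates.

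- Deaths: with the HFH hazard fixed so that one minus Kaplan-Meier is 15%, net death risks of 3%, 8% and 15% give an excess of 0.22, 0.59 and 1.12 points.
- HFH: with 3% dying first, HFH of 7% gives 0.11 points and HFH of 22% gives 0.37.

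**Against the trial's precision.** For 17.5% v 7.0% with 100 per arm, the simple binomial standard error of the difference is √(0.175 × 0.825/100 + 0.07 × 0.93/100) = 4.6 points. The added 0.63 points is 0.63/4.6, about 0.14 of one standard error.

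**The case against.** The strongest reply is that the point rests on inference and is small. Several stronger readings should be set aside.

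- **That the plan says deaths are censored.** It does not. SAP 8.4 is silent, and its wording is singular. The phrase in SAP Section 3 cannot be taken literally for every secondary endpoint either, since six-month echocardiographic response is not a time-to-event outcome. What stands is that HFH alone is naturally a time-to-event outcome, that no other such method is planned, and that a Kaplan-Meier curve for it has no other place to put deaths. If SAP 8.4 was meant for the composite only, HFH has no stated time-to-event method, and the text still needs a sentence.
- **That the HFH comparison is invalid.** A reader might infer this, but the log-rank test with deaths censored validly tests equality of the cause-specific HFH hazards. Only the curve, read as an absolute risk, is affected.
- **That a wrong HFH incidence will certainly be published.** No sentence says that one minus Kaplan-Meier will be quoted as the HFH rate. SAP 8.2 describes categorical variables by frequencies or percentages, and a crude percentage does not carry this bias, although it ignores unequal follow-up. The planned curve would carry it.
- **That the overstatement is always worse in the arm with more deaths.** This holds in relative terms, and in absolute terms when HFH rates are similar, but not generally. With 8% dying first and 2% HFH in LBBP, against 3% and 22% in BVP, the excess is 0.09 v 0.37 points, larger in the arm with fewer deaths.
- **That the trial's conclusion is at risk.** Death is an event in the primary composite and in all-cause mortality, so both are untouched, and no significance result is shown to change.

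**Conclusion.** The point holds in limited form. As written, the plan leads to a Kaplan-Meier curve for HFH alone that implicitly censors deaths, and one minus that curve overstates the probability of HFH. At the planned 25% and 10% composite rates the excess is about 0.7 points in BVP and 0.1 in LBBP, and it stays under 1 point per arm across the assumed range; even the extreme ordering of events keeps it under 2 points.

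The direction follows from the method. The size rests on an assumed death share and on proportional hazards, because the documents give no mortality or HFH rates. Severity is minor: a cheap improvement to the reporting of one secondary endpoint.

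**What to change.** In SAP 8.4, and in protocol section 11.2 for consistency:

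- State that, for HFH alone, all-cause death without a preceding HFH is a competing event.
- Plot and report HFH by the Aalen-Johansen cumulative incidence function in each arm.
- Keep the log-rank test for HFH, described as a comparison of cause-specific hazards, and add the cause-specific hazard ratio with its 95% CI.
- Keep Kaplan-Meier for the composite and for all-cause death.
- A Gray test or Fine-Gray model is optional and supportive only.

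The cost is a few sentences, slightly lower reported HFH rates, and possibly a second software package if the named SPSS version lacks the procedure. Visits, data collection and sample size do not change.

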## 8.5 Subgroup analysis

Subgroup analyses of the relationship between the primary endpoint and the baseline characteristics including age, sex, etiology, comorbidities, QRS duration, New York Heart Association (NYHA) class, and LVEF will be conducted.
